## Results

### Sample Size

The RCT of *myCompass* yielded an average between-group effect size on symptom outcomes of d=0.5 [25]. Van Bastellar et al [22] also reported controlled effect sizes of an online intervention for people with diabetes in the vicinity of d=0.5 for diabetes-related distress and depressive symptoms. Assuming an attrition rate of 50% [49,50], a total sample of 240 participants at follow-up (120 per arm) is the minimum required to detect between-group differences on self-report outcomes of .5 standard deviations with 80% power.

Nevertheless, we will aim for a final sample size 280 participants (140 per arm), as we have pilot data showing that this will enable us to detect a clinically meaningful decrease in HbA1c of 0.5% with power at 80%. This is based on analysis of clinic patients at Sydney Children’s Hospital, revealing a standard deviation of 1.04 for the change in HbA1c over 3 months. Recruitment is currently underway for this study.

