**Results:**

The primary outcome will be mental well-being (ie, depression, anxiety, diabetes-related distress, and positive well-being), for which data will be collected at baseline, post-intervention, and after 3 months follow-up. Secondary outcomes will be functional (work and social functioning and diabetes self-care), biochemical measures (HbA1c), and mental health self-efficacy. We aim to recruit 280 people into the study that will be conducted entirely online. Group differences will be analyzed on an intention-to-treat basis using mixed models repeated measures.

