### Statistical Analysis

Analyses will be completed with SPSS 22 software. Chi-squares (categorical variables) and *t* tests (continuous variables) will be used to compare demographic and disease-related variables and baseline scores on the outcome measures for the intervention and attention control groups. Similar analyses will be performed comparing participants who do (non-dropouts) and do not (dropouts) return completed questionnaires at each of the post-intervention and follow-up assessments to explore possible biases in study attrition.

Outcomes at each time point will be analyzed on an intention-to-treat basis using linear mixed modeling (LMM) [51], with time points as a within-group factor and intervention as a between-group factor. In LMM, incomplete cases are included in the analysis, and all available data is used to obtain parameter estimates. The interaction of time and study condition will be of primary interest in each analysis, with a significant interaction indicating a group difference in the pattern of change over time in the outcome of interest. Significant interactions will be explored using sets of Bonferroni adjusted comparisons of the two groups at post-intervention and 3-month follow-up. All effects will be tested at *P*<.05, with adjustment according to the number of contrasts in each set. Within- and between-group effect sizes will be calculated using Cohen’s d (based on the pooled standard deviation).

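### The stated minimum of 240 participants at follow-up does not follow from d=0.5 and 80% power, and recruiting 280 with 50% attrition cannot deliver it

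*Protocol article*

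**What the plan says.** The Sample Size section takes its effect size from an earlier trial of the same program, which "yielded an average between-group effect size on symptom outcomes of d=0.5". It assumes that 50% of participants will be lost. It then states that "a total sample of 240 participants at follow-up (120 per arm) is the minimum required to detect between-group differences"; the size of difference it has in mind is half a standard deviation, and the power is 80%. No alpha or sidedness is given there. The Statistical Analysis section says "All effects will be tested at *P*<.05". It qualifies that level as follows: "with adjustment according to the number of contrasts in each set". The sets in question are comparisons of the two groups at post-intervention and at 3 months.

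The next paragraph of the Sample Size section raises the number: "we will aim for a final sample size 280 participants (140 per arm"). The reason given is 80% power for an HbA1c decrease of 0.5%, with an SD of 1.04 for the 3-month change. The Results part of the abstract says "We aim to recruit 280 people into the study that will be conducted entirely online", and the Limitations section also gives 280 as the target.

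**The concern.** Two things do not fit. First, 120 per arm is far more than the usual requirement for d=0.5 at 80% power. Secondly, the article ties the 240 to follow-up while planning to recruit 280 and lose half of them, so its own assumptions put the stated minimum out of reach. The two paragraphs set 240 and 280 side by side as if they were on the same basis, although one is labelled as a follow-up count and the other works only as a count before attrition.

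The sample-size statement is the yardstick for judging retention and for reading a null result. With the wrong label on the 240, anyone monitoring follow-up would conclude that the trial had failed its own criterion when it had retained exactly what was planned.

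**Working it through.** **Inputs.** From Sample Size: d = 0.5, power 80%, attrition 50%, 240 at follow-up (120 per arm), 280 (140 per arm), HbA1c difference 0.5 with SD 1.04. From Statistical Analysis: alpha 0.05, Bonferroni-adjusted within each set of contrasts. Assumed: two-sided testing, equal arms, and a two-group comparison at one time point.

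**1. Number needed for d=0.5.** Per arm, n = 2(z₀.₉₇₅ + z₀.₈₀)²/d² = 2(1.960 + 0.842)²/0.25 = 62.8, so 63. The t test gives 63.8, so 64 per arm, or 128 in total. The plan's 240 is not reproduced.

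**2. Other alphas at 80% power (total with outcome data).**

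| Alpha | Normal approximation | t test |
|---|---|---|
| 0.05 one-sided | 100 | 102 |
| 0.05 two-sided | 126 | 128 |
| 0.025 (two contrasts) | 154 | 156 |
| 0.0125 (four primary outcomes) | 180 | 182 |
| 0.00625 (four outcomes × two contrasts) | 206 | 210 |

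None gives 240; that would take a two-sided alpha of about 0.0024. Some pairings with higher power do come to about 240 (for example two-sided 0.01 with 90% power), but they contradict the stated 80%.

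**3. What 120 per arm would give.** Power ≈ Φ(d√(n/2) − 1.960) = Φ(3.873 − 1.960) = 97.2%; the t test gives 97.1%. The difference detectable with 80% power would be d = 0.36.

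**4. Against recruitment.** 280 × 0.5 = 140 at follow-up, which is 240 − 140 = 100 below the stated minimum. Having 240 at follow-up would take 240/0.5 = 480 recruits.

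**5. 240 read as the number enrolled.** 240 × 0.5 = 120, or 60 per arm. Power ≈ Φ(2.739 − 1.960) = 78.2%; the t test gives 77.5%. The enrolment number for 80% is 128/0.5 = 256 (126/0.5 = 252 by the normal approximation).

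**6. What 280 is.** For HbA1c, n per arm = 2(1.960 + 0.842)² × (1.04/0.5)² = 67.9, so 68; the t test gives 69. At 50% attrition that is 272 to 276 enrolled, so 280 fits as the number randomised: 70 per arm gives 80.6% (t test). As a number of completers, 140 per arm would give 98.0%, which does not match the stated 80%.

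**7. Power of 280 randomised (70 per arm) for d=0.5, t test.** At two-sided 0.05: 83.6%. At 0.05/2 = 0.025, the level of the two pairwise contrasts: 75.5%. Reaching 80% at 0.025 needs 78 per arm with data, or 156/0.5 = 312 randomised.

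**The case against.** The best defence is that this is a misplaced label. The sentence opens with the attrition assumption, so 240 was probably already inflated for attrition and the follow-up wording was attached by mistake. The next paragraph replaces it with 280, which is the operative target. That is very likely what happened, and it stands as an explanation. It does not make the sentence right: the words are explicit, and as an enrolment number 240 is still about 6% below 256.

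A second defence is that the analysis is a linear mixed model over three time points, which may be more efficient than a t test. The article gives no correlation, so this can only be assumed. With 60 per arm against 63.8 needed, baseline adjustment would reach 80% if 1 − ρ² ≤ 60/63.8 = 0.94, that is ρ of about 0.24 or more. A change-score contrast would need 2(1 − ρ) ≤ 0.94, that is ρ of about 0.53 or more. So the 77.5% is not firm. This softens the criticism of 240 as an enrolment number only; it cannot make 240 the minimum at follow-up.

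Third, the word final in front of 280 is loose but not a second contradiction. Beside the abstract and the Limitations section it reads as the final recruitment target.

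**Conclusion.** The point holds as an error in a stated figure. For the inputs given, 240 at follow-up should be 128, and 240 is incompatible with recruiting 280 at 50% attrition. As an enrolment figure it falls short by 16 (256 − 240). These results assume a two-sided test at unadjusted 0.05 and a simple two-group comparison at one time point.

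A reader might go further in three ways that the article does not support:

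- **That the trial misses its required size by 42% (100/240).** This would be so only if 240 completers were needed, and they are not. With 280 randomised, power at unadjusted 0.05 is above 80% for both d=0.5 and HbA1c. The qualification is the Bonferroni-adjusted pairwise contrasts, where power for d=0.5 is about 75% before any gain from the mixed model.
- **That the recruitment target is unclear.** It is 280 wherever the article states a target; 256 and 480 are derived here and appear nowhere in it.
- **That the trial registration carries the same error.** The registry record was not available, so nothing can be said about it.

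**What to change.** In the Sample Size section:

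- Delete the statement that 240 at follow-up is the minimum.
- State that 128 participants with outcome data (64 per arm) are needed for d=0.5 with 80% power at unadjusted two-sided 0.05, which is 256 randomised at 50% attrition.
- Label 280 (140 per arm) as the number randomised, with about 140 (70 per arm) expected at follow-up.
- Give the resulting power together with its alpha: about 84% for d=0.5 and 81% for a 0.5% HbA1c difference (SD 1.04) at unadjusted two-sided 0.05, and about 75% for d=0.5 at 0.025 for the two pairwise contrasts. An 84% quoted without its alpha would not match the adjusted comparisons in the Statistical Analysis section.
- Add that these are simple two-group calculations that take no credit for the mixed model.

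The cost is a change of wording. Recruitment stays at 280.

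### The stated minimum of 240 for 80% power on self-report outcomes does not hold, whether 240 is read as recruited or retained, and is not tied to the planned analysis

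*Protocol article*

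**What the plan says.** The Sample Size section of the protocol article starts from an "average between-group effect size on symptom outcomes of d=0.5" in the earlier trial of the program. It continues "Assuming an attrition rate of 50" per cent, and gives the requirement as "a total sample of 240 participants at follow-up (120 per arm"). The claim made for that number is that it "is the minimum required to detect between-group differences on self-report outcomes of .5 standard deviations with 80% power". The section names no test, significance level, sidedness or repeated-measures correlation for this figure. It then raises the target on HbA1c grounds: "we will aim for a final sample size 280 participants (140 per arm").

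The Statistical Analysis section makes the time-by-condition interaction in a linear mixed model the effect of primary interest for each outcome. It adds: "Significant interactions will be explored using sets of Bonferroni adjusted comparisons of the two groups at post-intervention and 3-month follow-up". The level is set as follows: "All effects will be tested at *P*<.05". The article qualifies this for the contrasts, "with adjustment according to the number of contrasts in each set". With two assessments after baseline, a set of two contrasts implies .05/2 = .025 each. That value is inferred, not printed.

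**The concern.** The power sentence promises 80% for between-group differences and calls 240 the least number that achieves it. The analysis section looks for such differences by another route: an interaction test, then group contrasts at a stricter level. The power sentence mentions neither step. It is also unclear whether 240 counts people randomised or people still providing data, since attrition is assumed but the number is placed at follow-up.

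The figure sets the risk of missing a true 0.5 SD effect at 20%. If that risk is larger for a comparison at one assessment, a non-significant contrast there would be read as stronger evidence against the program than it is.

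**Working it through.** **Inputs.** d = 0.5, 80% power, 50% attrition, 240 and 280 (Sample Size); .05 and the two-contrast Bonferroni step (Statistical Analysis). Two-sided testing is assumed.

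**1. Trying to reproduce 240.** Normal approximation per arm: n = 2(1.960 + 0.842)²/0.5² = 62.8, so 63. The t test needs 64. Dividing by 1 − 0.5 gives 126 per arm (252 in all), or 128 per arm (256 in all) by t test. One-sided .05 gives 200 (204 by t test). None of these is 240.

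**2. Recruited or retained?** The HbA1c calculation in the same section helps: difference 0.5, SD 1.04, two-sided .05. With 70 completers per arm power is 80.6%; with 140 it is 98%. The stated 80% for 140 per arm therefore fits 140 before 50% attrition. The Abstract also describes 280 as the number to recruit. By analogy, 120 per arm is most likely recruited, leaving 60.

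**3. Two-group comparison, d = 0.5.** Noncentral t with noncentrality 0.5·√(n/2) and 2n − 2 df:

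| Completers per arm | Reading | Power at .05 | Power at .025 |
|---|---|---|---|
| 60 | 240 recruited | 77.5% | 68.0% |
| 70 | 280 recruited | 83.6% | 75.5% |
| 120 | 240 retained | 97.1% | 94.6% |

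For 80% at .025 the t test needs 78 completers per arm, or 312 recruited.

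**4. The planned mixed model.** Assumptions, none given in the article: SD 1, compound symmetry with correlation r from .3 to .7, baseline known for all N per arm, m = N/2 with data at both later assessments, effect 0.5 SD at both.

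The group difference at one later assessment has variance 2[(1 − r²)/m + r²/N].
- N = 120, r = .3: 2[0.91/60 + 0.09/120] = 0.0318, so effect/SE = 0.5/0.178 = 2.80.
- N = 120, r = .7: 2[0.51/60 + 0.49/120] = 0.0252, so effect/SE = 0.5/0.159 = 3.15.

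For the 2-df interaction, each change from baseline has per-arm variance (1 − r²)/m + (1 − r)²/N, and the two changes have covariance (r − r²)/m + (1 − r)²/N. With equal effects at both times the noncentrality is 2(0.5²)/[2(variance + covariance)].
- N = 120, r = .3: 0.5/[2(0.01925 + 0.00758)] = 9.3.
- N = 120, r = .7: 0.5/[2(0.00925 + 0.00425)] = 18.5.
- N = 140: multiply by 70/60, giving 10.9 and 21.6.

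Simulating the joint rule from these quantities gives, for r from .3 to .7:

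| Criterion | 240 recruited | 280 recruited |
|---|---|---|
| Interaction at .05 | 78–98% | 84–99% |
| Interaction plus at least one .025 contrast | 74–89% | 81–94% |
| Interaction plus the .025 contrast at one given assessment | 61–80% | 70–87% |

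At r = .5 the last row is about 69–71% and 78%. Repeat calculations agree within about two to three points.

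**The case against.** The strongest reply is that the trial as planned is adequately powered. The interaction at .05 is the effect of primary interest, and the Bonferroni contrasts only explore it. The target is 280, not 240. At 280, under the assumptions above, the interaction has at least 84%, and the interaction plus either contrast at least 81%, across the whole correlation range. This stands. A reader might infer that the whole study is underpowered for its self-report outcomes; the documents do not support that. Power below 80% at 280 appears only for a contrast at one pre-chosen assessment, and there only at the lower correlations.

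A reader might also blame the whole shortfall at 240 on the Bonferroni step. That fails too: 60 completers per arm are already four short of 64 at .05. Nor does the article single out the 3-month assessment, so the one-assessment figure describes one possible question, not the plan's success rule.

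Finally, a condensed article may leave alpha and correlation to a fuller document, and their absence is not the finding. The finding is that the printed minimum matches neither reading of its own inputs and is not the power of the analysis printed in the next section.

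**Conclusion.** The point holds in limited form. As a minimum for 80% power at d = 0.5 with 50% attrition, 240 is wrong: slightly too small if recruited (77.5% at .05; 256 needed) and far larger than necessary if retained (97%). For a group difference at a single assessment tested at .025, 240 recruited gives 68.0% by t test, or about 61–80% with the interaction required first in the mixed model. The planned 280 gives 75.5% and about 70–87%. The interaction test itself is adequately powered at 280.

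The t-test figures rest on two-sided testing and, for .025, on two contrasts per set. The mixed-model ranges also rest on the assumed correlation, compound symmetry, 50% missing at both later assessments, and an effect sustained at 0.5 SD. The results do not justify removing the interaction step or making one time point primary; that would be a design choice, not a correction.

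**What to change.** In the Sample Size section:

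- State whether 240 and 280 are recruited or retained.
- Replace 240 with the number that follows from the inputs: 256 recruited (128 per arm) for a two-sided t test at .05 with 50% attrition.
- Restate self-report power at the planned 280 for two quantities: the time-by-condition interaction at .05, and a Bonferroni-adjusted contrast at a single assessment. Give the alpha and the within-person correlation assumed.

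This takes two or three sentences. It needs no extra participants and no change of primary time point or analysis. The only cost is a slightly less favourable stated power for single-assessment contrasts.

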### Statistical Analysis

Analyses will be completed with SPSS 22 software. Chi-squares (categorical variables) and *t* tests (continuous variables) will be used to compare demographic and disease-related variables and baseline scores on the outcome measures for the intervention and attention control groups. Similar analyses will be performed comparing participants who do (non-dropouts) and do not (dropouts) return completed questionnaires at each of the post-intervention and follow-up assessments to explore possible biases in study attrition.

Outcomes at each time point will be analyzed on an intention-to-treat basis using linear mixed modeling (LMM) [51], with time points as a within-group factor and intervention as a between-group factor. In LMM, incomplete cases are included in the analysis, and all available data is used to obtain parameter estimates. The interaction of time and study condition will be of primary interest in each analysis, with a significant interaction indicating a group difference in the pattern of change over time in the outcome of interest. Significant interactions will be explored using sets of Bonferroni adjusted comparisons of the two groups at post-intervention and 3-month follow-up. All effects will be tested at *P*<.05, with adjustment according to the number of contrasts in each set. Within- and between-group effect sizes will be calculated using Cohen’s d (based on the pooled standard deviation).

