## Methods

### Study Design

A 2 (conditions) x 3 (time) RCT design is planned. Participants will be randomized to either the *myCompass* intervention or an active placebo intervention, and each group will have full program access for 7 weeks. Outcomes will be assessed at baseline, post-intervention (8 weeks), and three months follow-up (Figure 1).

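### Gating the arm comparisons on a free-baseline interaction test costs about 10 to 12 points of power for the post-intervention difference at the planned attrition; the tests remain valid

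*Protocol article*

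**What the plan says.** The Study Design section states: "A 2 (conditions) x 3 (time) RCT design is planned". It adds: "Outcomes will be assessed at baseline, post-intervention (8 weeks), and three months follow-up". Baseline is therefore one of the three levels of time.

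The Statistical Analysis section enters the factors into a linear mixed model "with time points as a within-group factor and intervention as a between-group factor" and states: "The interaction of time and study condition will be of primary interest in each analysis". The arm comparisons come second and only conditionally: "Significant interactions will be explored using sets of Bonferroni adjusted comparisons of the two groups at post-intervention and 3-month follow-up". On the error level: "All effects will be tested at *P*<.05, with adjustment according to the number of contrasts in each set". On missing data: "incomplete cases are included in the analysis, and all available data is used to obtain parameter estimates".

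The Sample Size section plans to "detect between-group differences on self-report outcomes of .5 standard deviations with 80% power", and mentions neither the interaction step nor the Bonferroni split. The Randomization section places allocation after baseline measurement. Table 1 gives every self-report outcome a score at screening or baseline, before allocation.

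**The concern.** The hypothesis under Study Aims and Hypotheses is directional: fewer symptoms and better well-being than control. A significant interaction on 2 degrees of freedom says that the arms changed differently somewhere across three times. It does not say in which direction or when. The arm comparisons at post-intervention and 3 months have to supply that, so their power matters as well as the interaction's.

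Those comparisons pay twice. They open only after a significant interaction, and they compare follow-up means from a model that estimates the baseline mean separately in each arm. Since randomisation follows baseline measurement, the true baseline means are equal, and estimating two of them adds noise. The plan expects 50% attrition, so it has little precision to spare.

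**Working it through.** **Inputs from the article.** Two arms, three times, d = 0.5, 80% power, 50% attrition, 240 (120 per arm) as stated minimum, 280 (140 per arm) as target, alpha .05, two contrasts per set, hence .025 each. Two-sided tests are assumed because sidedness is not stated.

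**Assumed, because the article does not give them.** Correlations between visits, written baseline–post / baseline–3 months / post–3 months; SD 1 at each visit; d = 0.5 at both follow-ups; N = 140 randomised and n = 70 observed per arm, with dropouts contributing baseline only.

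**The plan's own calculation.** For one unadjusted comparison at .05, power is Φ(d√(n/2) − 1.960).
- 60 completers per arm (half of 120): Φ(2.739 − 1.960) = 78.2%, close to the stated 80%. The formula itself needs 63 per arm, or 252 randomised, a small separate mismatch.
- 70 completers per arm: Φ(2.958 − 1.960) = 84.1%.

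Neither figure includes the gate or the Bonferroni split.

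**Variance of the post-intervention difference**, with r the baseline–post correlation:
- completers only: 2/n
- planned model, free baseline means: 2[(1 − r²)/n + r²/N]
- common baseline mean: 2(1 − r²)/n

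At r = 0.5 these are 2/70 = 0.0286; 2[0.75/70 + 0.25/140] = 0.0250; and 2 × 0.75/70 = 0.0214. The planned model already recovers (0.0286 − 0.0250)/(0.0286 − 0.0214) = half of the available gain, through dropouts' baseline scores. In general the share is 1 − n/N. The ratio of constrained to planned variance is 0.95, 0.86, 0.78 and 0.68 at r = 0.3, 0.5, 0.6 and 0.7.

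**Power without the gate, at .025** (critical value 2.241), r = 0.5:
- planned model: Φ(0.5/0.1581 − 2.241) = Φ(0.921) = 82%
- common baseline: Φ(0.5/0.1464 − 2.241) = Φ(1.174) = 88%

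**Whole decision path**, by large-sample simulation with 400,000 draws. The planned path requires the 2-df interaction at .05 and then the post-intervention contrast at .025.

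| Correlations | Interaction alone | Planned path, post | Free baseline, no gate, post | Common baseline, no gate, post | At least one common-baseline contrast |
|---|---|---|---|---|---|
| .3/.3/.3 | 85% | 71% | 78% | 81% | 94% |
| .5/.4/.6 | 88% | 76% | 82% | 88% | 95% |
| .6/.5/.7 | 92% | 81% | 85% | 93% | 97% |
| .7/.6/.7 | 98% | 87% | 88% | 97% | 99% |

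At .5/.4/.6 the 12-point gap splits evenly: about 6 points from the gate (82 to 76) and 6 from the baseline constraint (82 to 88). At low correlation most of the loss is the gate; at high correlation most of it is the baseline.

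**No true effect.** The interaction rejects in 5.0% of trials. The ungated adjusted pair declares a difference at either time in 4.5 to 4.9%.

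**Sensitivity.**
- Effect fading to d = 0.25 at 3 months, .5/.4/.6: 74% against 88%.
- All 120 per arm observed, d = 0.5 at both times: 89% against 97% at .3, 92% against 99% at .5/.4/.6, 95% against nearly 100% at .7/.6/.7.
- All 140 per arm observed: the gap is 3 to 4 points.

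**The case against.** The strongest reply is that the interaction, not the arm comparisons, is the named primary test. It uses every baseline score, holds its level and has 85 to 98% power in the table above, which exceeds the 80% target. An omnibus test followed by simple comparisons is also a conventional sequence. All of that stands, and it is why this is a point about efficiency. It does not remove the point, because the interaction alone cannot show the direction that the hypothesis asserts. Even on the looser question of finding any difference, it trails the pair of adjusted contrasts (85 to 98% against 94 to 99%).

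A reader might infer three stronger things that the documents do not support.
- **That the comparisons ignore baseline.** This is exact only with complete data. With 50% loss the planned mixed model recovers half the gain.
- **That most of the 5% error is wasted.** Under no effect, 1.3 to 2.0% of trials pass both the interaction and a contrast. That is the joint rate of two steps; the primary test still spends its full 5%.
- **That chance baseline imbalance biases the result, or that the two steps estimate different effects.** Imbalance is already in the standard error. With equal true baselines, the difference in change and the difference in level have the same expected value. They differ in precision.

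Two further reservations also stand. Enrolment on PHQ-9 and DDS cut-offs may lower the correlation for those outcomes. The Sample Size section can also be read literally as 120 or more per arm observed at follow-up, which shrinks the loss. A condensed article might leave a covariate to the analysis plan, but here the factors, the gate and the contrasts are all stated.

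**Conclusion.** The point holds as a should-fix loss of efficiency. With 140 randomised and 70 observed per arm and d = 0.5 at both follow-ups, power to declare the post-intervention difference is 10 to 12 points lower than the same data allow, over assumed correlations from 0.3 to 0.7. The baseline-constrained contrast did better at every correlation tried. The loss grows if the effect fades by 3 months. With a sustained effect it falls to about 5 to 8 points if 120 per arm are observed and 3 to 4 if 140 are. The correlations and the observed number are assumptions, so the exact size is uncertain. No bias or inflated error rate was found.

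**What to change.** - Fit the same mixed model with one common baseline mean for both arms. Alternatively, use post-intervention and 3-month scores as outcomes, with baseline score and baseline-by-time as covariates. The first form keeps participants who give only a baseline score in the model.
- Pre-specify the adjusted arm differences at post-intervention and 3 months as the confirmatory contrasts for each outcome, each at .025, without requiring a significant interaction. Error over the two times stays below 5%; this split does not address multiplicity across outcomes.
- Keep the interaction as a descriptive test of the pattern over time.
- Compute the between-group d from the adjusted differences, divided by the pooled raw-score SD so that it stays comparable with the 0.5 used for sizing.

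The cost is a few lines of model syntax and analysis wording, with no new data or participants. The Sample Size section says recruitment is under way, so the change should be recorded before outcome data are examined by arm.
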